##### Primary endpoint analysis

The primary endpoint is the proportion of patients tested positive for SARS-CoV-2 amongst the flow of consulting adults. The denominator is a number of patients in the emergency departments (and not the number of tests performed).

Patients considered positive for SARS-CoV-2 will be those with a positive test result and whose SARS-CoV2+ status is not known. Patients considered non-positive for SARS-CoV-2 will be patients not tested, patients tested negative or with an undeterminate result and patients tested positive with a known SARS-CoV2+ status.

The primary analysis will be performed according to the intent-to-treat (ITT) principle. The primary outcome will be analysed using a generalised linear mixed model (Poisson distribution or any other distribution adapted to the data) with the centre as a random intercept and the strategy, the period and the period x strategy interaction as fixed effects. The incidence of SARS-CoV2 or the evolution of the epidemic over time will be taken into account if appropriate. Fixed variables could be added to the model if appropriate.

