##### Secondary endpoints analyses

- The proportion of patients tested positive for SARS-CoV-2 among the asymptomatic or paucisymptomatic patients tested by nurses and that in the Paris Metropolitan area at the same period will be compared using an asymptotic Wald test.  
The proportion obtained in each emergency department will be compared to that of the department's IRIS geographical area using an asymptotic Wald test. The same comparisons will be made across the entire tested population.
- The feasibility of the testing will be described: proportion of patients who have completed the questionnaire, proportion of offered, accepted and performed tests, and notified of the SARS-CoV-2 result and staff involved (nurses, caregivers, doctors, others),
- The proportion of patients tested positive for SARS-CoV-2 among the patients tested by nurses, the proportion of asymptomatic patients among the patients tested by nurses and the proportion of asymptomatic patients among the patients tested positive for SARS-CoV-2 will be described.

|                        |              |
|------------------------|--------------|
| Study                  | DEPIST-COVID |
| Promotion/gestion code | APHP201625   |
| Study coordinator      | [name]   |

- The symptoms of patients tested positive for SARS-CoV-2 will be described in the patients completed the questionnaire.
- Exposure factors will be described using the items in the DEPIST-COVID questionnaire. Among patients tested, the exposure factors associated with the positivity of the SARS-CoV-2 test will be analysed using a generalised linear mixed model (binomial distribution or other distribution adapted to the data). The exposure factors will be considered as fixed effects and the site as a random intercept. Other fixed variables could be added to the model if appropriate.
- The sociodemographic, behavioural and practical factors of diagnosed patients associated with positive SARS-CoV-2 infection will be described for the schemes (DEPIST-COVID, ComCor) according to the types of variables (proportion, mean and standard deviation or median, Q1-Q3) and presented with their 95% confidence interval. If appropriate, the factors will also be analysed in the population of DEPIST-COVID cases (positive tested patients) and controls (negative and matched tested patients).

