## Changes to the analysis plan

### **Primary endpoint analysis**

The primary outcome will be analysed using a generalised linear mixed model (Poisson distribution or any other distribution adapted to the data) with the centre as a random intercept, the centre-by-period interaction as random effect and the strategy, the period and the incidence rate-by-period interaction as fixed effects. The logarithm of the number of patients will be included as an offset term in the model.

The period will be modelled as weekly (1 to 15).

Patients considered non-positive for SARS-CoV-2 will be patients not tested, patients tested negative or with an undeterminate result and patients tested positive with a known SARS-CoV2+ status for less than 3 months.

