### **Secondary endpoints analyses**

- Factors associated with performing systematic nurse-driven screening will be analysed in patients who had screening offer using a generalised linear mixed model (binomial distribution) with the centre as a random intercept and the patient characteristics as fixed effects.

- The factors associated with new SARS-CoV-2 diagnoses will be analysed using a generalised linear mixed model (binomial distribution) with the centre as a random intercept and patient characteristics as fixed effects.

- The proportions of new SARS-CoV-2 diagnoses through systematic nurse-driven screening overall and per ED, and proportion among all patients tested in EDs, will be compared to the proportion of positive tests among adults tested in the geographical departments of the Paris Metropolitan area using the Miettinen-Nurminen method for risk difference and 95% CI estimations.

[figure not shown]

Coller ici l'étiquette patient

N° DOSSIER :

\_\_\_\_\_  
Centre

\_\_\_\_\_  
Patient

PLEASE FILL OUT THIS QUESTIONNAIRE BY CHECKING THE SQUARE  
CORRESPONDING TO YOUR RESPONSE [figure not shown]

1 You are:

☐ male ☐ female

2 What is your date of birth?

Month Year

3 Do you have symptoms suggestive of Covid-19?

☐ Yes ☐ No

> If yes, please precise:

☐ Fever (>38°C)  
or fever sensation

☐ Cough

☐ Loss of smell

☐ Muscular pain

☐ Unusual fatigue

☐ Breathing difficulty  
(shortness of breath)

☐ Loss of taste

☐ Other

☐ Headache

☐ Sore throat

☐ Diarrhoea

☐ Runny nose

> If yes, date of first symptoms:

Day Month Year

4 What is your postcode?

5 In which country were you born?

☐ France

☐ Other

Please specify your country of birth:

6 Until what age did you study?

years

7 Currently (over the last month):

☐ You work

☐ You do not work

☐ You are seeking employment

☐ You are a student

> If you work:

• Do you work away from home?:

☐ Yes

☐ No

☐ Partially

• Does your occupation expose you to contacts with:

- Members of the public?

☐ Yes

☐ No

- Sick persons?

☐ Yes

☐ No

8 What is your medical coverage:

☐ Social security without supplementary health insurance

☐ CMU (Universal medical cover)

☐ Social security with supplementary health insurance

☐ AME (State medical assistance)

☐ No medical coverage

☐ Other

9 Do you suffer from a chronic disease (diabetes, high blood pressure, angina pectoris, chronic bronchitis, asthma or chronic respiratory disease)?

☐ Yes

☐ No

10 Do you currently smoke cigarettes?

☐ Yes

☐ No

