\*\*\* For this variable of the DEPIST-COVID questionnaire: data were collected in 8 centers, and it was not possible to collect them later in the remaining 10 centers. Findings are presented for 8 centers (n=2,226 patients, missing data: 19.5% in the 8 centers).

Q1: First quartile; Q3: Third quartile; CI: Confidence interval.

Appendix E. Table Characteristics of patients tested through SARS-CoV-2 screening for asymptomatic/paucisymptomatic patients

Table E1. Characteristics of patients tested through SARS-CoV-2 screening for asymptomatic/paucisymptomatic patients

|                                                   | Total population
N=4 192* |                                | New SARS-CoV-2
diagnoses
n=224 |                             | Negative SARS-CoV-2
tests
n=3 968 |                             | Risk difference            |
|---------------------------------------------------|------------------------------|--------------------------------|--------------------------------------|-----------------------------|-----------------------------------------|-----------------------------|----------------------------|
|                                                   | N                            | n (%)
or median [Q1,
Q3] | N                                    | n (%)
or median [Q1, Q3] | N                                       | n (%)
or median [Q1, Q3] | %
or median
(95% CI) |
| Age (years)                                | 4166                         | 41.0 [29.0, 56.0]              | 224                                  | 46.0 [31.0, 63.5]           | 3942                                    | 40.0 [29.0, 55.0]           | 6.0 (1.6, 10.4)            |
| Sex                                        | 4187                         | .                              | 224                                  | .                           | 3963                                    | .                           |                            |
| Female                                            | .                            | 1900 (45.4)                    | .                                    | 97 (43.3)                   | .                                       | 1803 (45.5)                 | -2.2 (-8.7, 4.5)           |

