| Hospitalization                                                                              | .                            | 24 (1.8)                       | .                                    | 2 (5.6)                     | .                                       | 22 (1.7)                    | 3.9 (-0.3, 16.5)            |
| Only emergency department visit: outpatients                                                 | .                            | 1304 (98.2)                    | .                                    | 34 (94.4)                   | .                                       | 1270 (98.3)                 | -3.9 (-16.5, 0.3)           |
| Among patients with rapid multiplex respiratory virus test, other respiratory viruses | 581                          | .                              | 116                                  | .                           | 465                                     | .                           | .                           |
| Yes*****                                                                                     | .                            | 77 (13.3)                      | .                                    | 5 (4.3)                     | .                                       | 72 (15.5)                   | -11.2 (-15.7, -5.2)         |

\* Patients with indeterminate results or a known positive SARS-CoV-2 status were not included in this table. In univariate analysis, factors associated with new infections diagnosed through screening for asymptomatic/paucisymptomatic patients were mainly older age, having mild symptoms, not being from France, particularly being from Sub-Saharan Africa, being unemployed, not having medical coverage, living in a community, being a case contact and not being previously screened.

\*\* Among patients who underwent a rapid molecular SARS-CoV-2 test, 258 (7.4%) reported having symptoms. Among patients who underwent a rapid multiplex respiratory virus test, 508 (90.1%) reported having symptoms.

\*\*\* Chronic diseases: diabetes, arterial hypertension, angina pectoris, chronic bronchitis, asthma or chronic respiratory disease

\*\*\*\* For this variable of the DEPIST-COVID questionnaire, data were collected in 8 centers, and it was not possible to collect them later in the remaining 10 centers. Findings are presented for 8 centers (n=1,510 patients, missing data: 12.1% in the 8 centers).

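### The ED-versus-community comparison sets new diagnoses in the ED against positive tests in the community, and counts 91 ED patients with an indeterminate or known-positive result as not positive

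*Combined protocol and SAP*

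**What the plan says.** In the Changes to the analysis plan (Secondary endpoints analyses), the ED quantity is "The proportions of new SARS-CoV-2 diagnoses through systematic nurse-driven screening overall and per ED", together with the proportion among all patients tested in EDs. It is "compared to the proportion of positive tests among adults tested in the geographical departments of the Paris Metropolitan area". The plan obtains the estimate and its interval "using the Miettinen-Nurminen method for risk difference and 95% CI estimations".

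The rule for known cases appears only under the primary endpoint. Final SAP 1.1 counts as non-positive "patients tested positive with a known SARS-CoV2+ status". The Changes to the analysis plan narrow this to "patients tested positive with a known SARS-CoV2+ status for less than 3 months".

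The secondary endpoint text of Final SAP 1.1 words the ED side differently: "The proportion of patients tested positive for SARS-CoV-2 among the asymptomatic or paucisymptomatic patients tested by nurses".

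The results are in Appendix J: Table J1 (screened ED patients overall), J2 (per ED) and J3 (all ED tests). The note to Table E1 in Appendix E says: "Patients with indeterminate results or a known positive SARS-CoV-2 status were not included in this table".

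**The concern.** A difference between two proportions can be interpreted only if both sides count the same event over the same kind of denominator. Here a patient who tests positive but whose infection is already known is not an event on the ED side. Nothing in the documents says that such a person is left out of the community count. An ED test without a usable result also appears to stay in the ED denominator.

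Protocol 2.2 expects positivity among asymptomatic ED patients to exceed that of the region, and this comparison is the first secondary endpoint in Protocol 4.2. The lower confidence limit in Table J1 is 0.01 points, so a small change of definition matters to how the result reads.

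**Working it through.** **Inputs**
- Table J1, ED: 4,283 tested, 224 Yes, 4,059 No. Community: 156,298 of 3,400,584. Reported difference 0.6 (0.01, 1.3).
- Table E1: 4,192 patients, of whom 224 are new diagnoses; the remaining column is "Negative SARS-CoV-2 tests n=3 968".
- Table D1 (screening performed, n = 4,283) against Table E1 (n = 4,192): dated prior positive test, 223 against 198. Answered the item on prior Covid testing, 3,877 against 3,798; of these, yes 2,263 against 2,196.

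**1. Reproduce the published figure.** 224/4,283 = 5.23% and 156,298/3,400,584 = 4.60%. The Miettinen-Nurminen interval for the difference is 0.63 points (0.006 to 1.34), which matches Table J1. A Wald interval would be -0.03 to 1.30.

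**2. Locate the patients counted as No.** 4,059 - 3,968 = 91 and 4,283 - 4,192 = 91. The No row of Table J1 therefore holds 91 patients who are not among the negative tests of Table E1. By the note to that table they had an indeterminate result or a known positive status. The numerators and denominators of Table J2 sum to 224 and 4,283, so the same 91 are also in the per-ED comparison.

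**3. Recompute on a positive-test definition.** Let k of the 91 be positive tests with a known status and 91 - k be indeterminate. With all positive tests over all interpretable tests, the ED proportion is (224 + k)/(4,192 + k).

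| Assumed k | ED proportion | Difference, points (95% CI) |
|---|---|---|
| As published | 224/4,283 = 5.23% | 0.63 (0.01 to 1.34) |
| 0 | 224/4,192 = 5.34% | 0.75 (0.11 to 1.47) |
| 25 | 249/4,217 = 5.90% | 1.31 (0.64 to 2.06) |
| 67 | 291/4,259 = 6.83% | 2.24 (1.52 to 3.03) |

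Every value of k gives a proportion above 5.23%, so the direction is settled and the size is not.

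**4. What the tables say about k.** Dated prior positives fall by 223 - 198 = 25. Median time since the prior positive rises from 137 to 148 days and the first quartile from 56 to 70 days, which suggests that some recent positives were removed. This does not fix k. In Table E1, 192 of the 198 patients with a dated prior positive tested negative, so a prior positive does not imply a positive retest.

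Of the 91, 3,877 - 3,798 = 79 answered the prior-testing item and 2,263 - 2,196 = 67 said yes. The other 79 - 67 = 12 are tabulated as never tested before. At face value that argues against all 91 being known positives (315/4,283 = 7.35%).

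**5. If the community source already drops known cases.** The numerators would then agree, and only the ED denominator is at issue: 5.23% to at most 5.34%.

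**6. Symptom mix.** Table J1 compares asymptomatic or paucisymptomatic ED patients with asymptomatic community adults. In Table E1, 133 of 216 new diagnoses and 766 of 4,062 tested patients reported symptoms. Without them, (216 - 133)/(4,062 - 766) = 83/3,296 = 2.52%, a difference of -2.08 points (-2.55 to -1.49).

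**The case against.** The new-diagnosis numerator has a clear rationale. The study aims to find people unaware of their infection (Protocol 2.1.4.1), and re-detecting a known case is not yield. The titles of Tables J1 to J3 name both quantities openly. Against a broader comparator the choice is conservative, and in the scenarios of step 3 neither the sign of the J1 difference nor the exclusion of zero changes. This supports the numerator for the primary endpoint and as an extra description here. It does not make the two sides comparable, and it does not justify counting indeterminate tests as negative.

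The documents also never say how the community source handles repeat positives. They give a label and a data provider. This stands, and it limits the point to the assumption stated in the verdict.

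Three stronger readings are tempting, and the documents support none of them:
- A reader might infer that the signed SAP meant all positives, known cases included, and that the later change replaced that numerator. The secondary text of Final SAP 1.1 does not define the phrase, and the primary endpoint text of the same SAP excludes known cases. The change may only spell out that definition.
- A reader might take the k = 25 row to show that the difference is really twice the published one. It is an illustration. It assumes that all 25 retested positive and that the other 66 were indeterminate.
- A reader might conclude that the true ED excess is larger than published. Step 6 shows a separate imbalance that works in the opposite direction, so no net understatement is shown.

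**Conclusion.** The comparison is wrong as written: its two sides use unmatched definitions, and Table J1 counts as not positive 91 ED patients who did not have a negative test. On a positive-test definition the ED proportion is at least 5.34% rather than 5.23%, and the difference at least 0.75 points (0.11 to 1.47) rather than 0.63 (0.01 to 1.34). How much more depends on the unpublished split of the 91.

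This rests on one assumption, that the community source does not drop repeat or known positives. If it does, what remains is the denominator effect, up to 5.34%. Table J3 uses the same kind of numerator (3,943 new diagnoses of 40,367 tested), but its number of known positives is not given and no size can be put on it.

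Confidence is moderate. The point concerns one secondary comparison and leaves the primary endpoint untouched.

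**What to change.** For this comparison, define the ED proportion as all positive ED tests, whatever the known status, over all interpretable ED tests, with indeterminate results removed. Apply it overall, per ED and to all patients tested. Report how the 91 divide into indeterminate results and known positives, and state how the community data treat repeat positives.

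Keep new diagnoses for the primary endpoint. If a new-diagnosis version is also shown here, remove known positives from both numerator and denominator and label it as not matched to the community source.

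The cost is a short change to the SAP, a question to the data provider, and a rerun of Tables J1 to J3. The exclusions in Table E1 show that the status of screened patients has already been classified. For Table J3 the same classification would have to be confirmed for all ED tests.

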|--------------------------------------------------------|---------------------------------------------------------------------------------------------------------------------------------------------------------------------------------------------------------------------------------------------------------|
| Number of inclusions expected per centre and per month | 2889                                                                                                                                                                                                                                                    |
| Statistical analysis                                   | There is no interim analysis planned. The analysis will be performed at the end of the research after the data review meeting and freezing of the database, according to the intention-to-treat principle and taking into account cluster randomisation |
| Source of funding                                      | ANRS [Agence Nationale de la Recherche (National Research Agency)] – REACTing and the AP-HP                                                                                                                                                             |

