## 5.2 Number of participating sites

The multicentre research will involve 18 emergency departments in the Paris Metropolitan area (see addendum 1).

In each hospital participating in the research, a virologist contact will be identified to facilitate the collection of virology data.

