|                              |                  | 13321 (3.0) |                                                                                   | 2 (1.4)   |                                                                             | 13319 (3.0) | -1.7 (-2.6, 1.8)                                |
| Center 18                    | 383530           |             | 135                                                                               |           | 383395                                                                      |             |                                                 |
|                              |                  | 7680 (2.0)  |                                                                                   | 4 (3.0)   |                                                                             | 7676 (2.0)  | 1.0 (-0.8, 5.4)                                 |

\* Source: Community screening data were provided by Santé publique France on May 20, 2022.

For each emergency department (ED) taken separately, the proportion of new infections diagnosed through ED screening for asymptomatic/paucisymptomatic patients was higher for 3 EDs compared to the proportion of positive tests among asymptomatic individuals tested in the corresponding geographical department.

- c. Table J3. New SARS-CoV-2 diagnoses through screening in emergency departments and positive tests through community screening for adults in the geographical departments of the Paris metropolitan area during the same period

| SARS-CoV-2
positive tests | Total population |                | SARS-CoV-2 screening
in EDs |              | Community screening for
SARS-CoV-2 in the Paris
metropolitan area* |                | Risk difference
(95% Confidence
interval) |
|------------------------------|------------------|----------------|--------------------------------|--------------|--------------------------------------------------------------------------|----------------|-------------------------------------------------|
|                              | N                | n (%)          | N                              | n (%)        | N                                                                        | n (%)          |                                                 |

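### The interval for ED versus community positivity ignores variation between the 18 EDs; once that variation is counted, it no longer excludes zero

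*Combined protocol and SAP*

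**What the plan says.** The signed final SAP (1.1, Secondary endpoints analyses) takes the proportion positive among asymptomatic or paucisymptomatic patients tested by nurses and states that this and "that in the Paris Metropolitan area at the same period will be compared using an asymptotic Wald test". The section headed Changes to the analysis plan replaces that test: the ED proportions, overall and per ED, are compared with community testing "using the Miettinen-Nurminen method for risk difference and 95% CI estimations". Neither text mentions centre, clustering or a design effect for this comparison.

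Other parts of the plan do account for centre. The model for factors associated with new diagnoses, in the same list, is fitted "with the centre as a random intercept and patient characteristics as fixed effects", and the synopsis says the analysis will be done "according to the intention-to-treat principle and taking into account cluster randomisation". Protocol 5.2 states: "The multicentre research will involve 18 emergency departments in the Paris Metropolitan area".

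The results are in Appendix J. Table J1 gives 224/4,283 (5.2%) in EDs against 156,298/3,400,584 (4.6%) in the community, a difference of 0.6 points (0.01 to 1.3). Table J2 gives the same comparison for each ED against its own geographical department.

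**The concern.** The Wald and Miettinen-Nurminen methods both assume two samples of independent binomial observations. Patients screened in one ED share a catchment, a calendar window, a nursing team and a way of choosing whom to test. If positivity differs between EDs by more than chance, 4,283 patients from 18 EDs carry much less information than 4,283 independent patients, and the interval is too short.

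This is the first-listed secondary endpoint (protocol 4.2), and protocol 2.2 expects a higher rate in the ED population. The only overall evidence for that expectation in Appendix J, Table J1, is an interval with a lower limit of 0.01 points, so even modest clustering would change how it reads.

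**Working it through.** **Inputs (Table J2).** Here x is ED positives, n is ED patients screened, q is the community proportion in the ED's own department (computed from the counts), and E = n × q.

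| Centre | x/n | ED % | q % | E |
|---|---|---|---|---|
| 1 | 23/429 | 5.4 | 3.5 | 14.9 |
| 2 | 10/357 | 2.8 | 3.6 | 12.7 |
| 3 | 2/129 | 1.6 | 3.7 | 4.8 |
| 4 | 11/176 | 6.3 | 3.6 | 6.3 |
| 5 | 14/269 | 5.2 | 6.3 | 17.1 |
| 6 | 13/201 | 6.5 | 8.4 | 16.9 |
| 7 | 15/322 | 4.7 | 6.4 | 20.7 |
| 8 | 4/149 | 2.7 | 3.9 | 5.8 |
| 9 | 19/345 | 5.5 | 4.6 | 16.0 |
| 10 | 7/152 | 4.6 | 5.0 | 7.6 |
| 11 | 23/198 | 11.6 | 8.3 | 16.4 |
| 12 | 11/136 | 8.1 | 4.6 | 6.2 |
| 13 | 5/173 | 2.9 | 3.7 | 6.3 |
| 14 | 10/281 | 3.6 | 3.2 | 8.9 |
| 15 | 49/331 | 14.8 | 7.5 | 24.9 |
| 16 | 2/353 | 0.6 | 2.6 | 9.3 |
| 17 | 2/147 | 1.4 | 3.0 | 4.4 |
| 18 | 4/135 | 3.0 | 2.0 | 2.7 |
| Sum | 224/4,283 | 5.2 | | 201.9 |

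**1. Reproduce the reported figure.** The independent-binomial Miettinen-Nurminen interval on 224/4,283 against 156,298/3,400,584 is 0.634 points (0.006 to 1.342), which rounds to the published 0.6 (0.01, 1.3). All 18 single-ED intervals reproduce in the same way, so no clustering was applied.

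**2. Is positivity homogeneous across EDs?** Against the pooled rate p = 0.0523, Σ(x - np)²/[np(1 - p)] = 115.7 on 17 df. Part of this is local epidemic level, because q itself runs from 2.0% to 8.4%. Against each department's own rate, Σ(x - E)²/[nq(1 - q)] = 55.2 on 18 df (p about 1 × 10⁻⁵). If E is first rescaled to total 224, the figure is about 45 on 17 df. Real between-ED variation remains.

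**3. Cluster the pooled comparison by ED.**
- Independent SE = √[0.0523 × 0.9477/4,283] = 0.340 points.
- Cluster-robust SE = √[(18/17) × Σ(x - np)²]/4,283 = √[(18/17) × 1,657.4]/4,283 = 0.978 points.
- Ratio 0.978/0.340 = 2.88, a design effect of 8.3.
- 95% CI with t on 17 df: 0.634 ± 2.110 × 0.978 = -1.43 to 2.70, which is 3.1 times as wide as the reported interval.
- Cross-checks: an ANOVA intracluster correlation of 0.025 with a size-weighted mean cluster size of 276 gives a design effect of 7.8 (SE factor 2.79). A cluster bootstrap gives -1.03 to 2.65.

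**4. Match each ED to its own department.**
- D = (224 - 201.9)/4,283 = 0.52 points.
- SE = √[(18/17) × Σ(x - E - nD)²]/4,283 = √[(18/17) × 837.6]/4,283 = 0.695 points.
- 95% CI: 0.52 ± 2.110 × 0.695 = -0.95 to 1.98. Its width is 2.93 points against 1.34 reported, a ratio of 2.2.

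**5. Sensitivity.**
- With the primary outcome's reported correlation of 0.0035 (Appendix I), the SE factor is only 1.4 and the interval about -0.30 to 1.57.
- Without Centre 15, observed is 175 and expected 177.0. This drops the most extreme ED after seeing the data, so it shows where the excess lies and is not an alternative estimate.

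Community rates are treated as fixed. The sampling error of the pooled rate is about 0.01 point, and the Table J2 community counts overlap between EDs.

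**The case against.** The strongest reply is that the 18 EDs were not sampled. Protocol 2.3 says they were chosen for recruitment capacity and motivation, and for inference restricted to these EDs a stratified SE is 0.336 points, no larger than the independent 0.340. That is correct for that narrow question. However, the protocol looks beyond these sites: the synopsis speaks of representing the region's population, 2.1.4.1 speaks of replicating the strategy, and the plan's other models treat centre as random. Even on the restricted reading, the department-matched interval is 0.52 ± 1.96 × 0.336 = -0.14 to 1.17, which includes zero.

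A second reply is that a patient-level random-intercept model does not carry over directly to a comparison with aggregate surveillance counts. This also stands, but an ED-level observed-versus-expected analysis needs only the counts in Table J2.

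A reader might be tempted to go further in four ways that the documents do not support:
- **The change from Wald to Miettinen-Nurminen produced the result.** On 4,283, Wald does give -0.03 to 1.30. On the 4,192 patients of Table E1, which leaves out indeterminate results and known positives, Wald gives 0.07 to 1.43 and also excludes zero. The change is openly listed.
- **Eighteen unadjusted comparisons are an error.** The plan asks for estimates with intervals on a secondary endpoint, and Table J2 has no p-values. Whether to adjust is a matter of preference.
- **Centre 16 was concealed.** The note says only that positivity "was higher for 3 EDs compared to the proportion of positive tests among asymptomatic individuals tested in the corresponding geographical department", but the table prints Centre 16 in bold as -2.1 (-2.5, -0.6).
- **The trial concludes that ED screening finds more infections overall.** These documents state an expectation and report tables. They contain no such conclusion.

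**Conclusion.** The concern holds for the interval. The planned method omits between-ED variation that is plainly present in the trial's own counts, and the reported 0.01 to 1.3 overstates precision. How much depends on the comparison. The interval should be about three times as wide for the pooled, unmatched comparison as planned, and about 2.2 times for the department-matched one, so a general statement that it is three times too narrow would go too far. Zero lies inside every clustered version examined, including the one with the small correlation of 0.0035. Using 4,192 raises the difference to 0.75 points, and a clustered SE near 1 point would still leave zero inside.

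This rests on two assumptions: that inference is meant to reach beyond these 18 EDs, and that the Table J2 community counts cover each ED's own study dates. Appendix J's title refers to the same period, and the denominators differ between inner-Paris EDs, which fits the second assumption. The endpoint is secondary and non-randomised. The primary analysis models centre and is not affected.

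**What to change.** In Changes to the analysis plan, Secondary endpoints analyses, replace the method for the overall comparison with an ED-level comparison of observed and expected positives. Take the expected count as patients screened times the community proportion for the same department and dates, as in Table J2. Give a 95% CI that is cluster-robust (t, 17 df) or comes from a random-effects model with ED as the unit. State that the EDs are treated as a sample of a wider set. Keep the 18 single-ED differences, labelled as descriptive.

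Report the result on both 4,283 and 4,192. The second needs per-ED counts that are not in the appendices but should be in the database.

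The cost is a paragraph of SAP wording and a short re-analysis of tables already produced, with no new data collection. The downside is a wider interval that no longer excludes zero.
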